### Statistical methods for investigated endpoints

The efficacy analysis will be performed on the modified Full Analysis Set defined as all patients receiving radiotherapy with a completed questionnaire at baseline and at least one completed questionnaire after start of treatment. Similar to a previous study, the statistical analyses are mainly descriptive and exploratory [10]. Sleep disorders at baseline and during radiotherapy will be rated using two patient self-reporting scales (sleep disorders and distress) and intake of sleeping drugs. To evaluate the rate of patients with decrease of sleep disorders after 15 fractions of radiotherapy (generally at the end of the third week of treatment), the dichotomized composite endpoint (decrease of severity of sleep disorders, decrease of distress caused by sleep disorders, reduction of the dose of sleeping drugs) is considered, even if patients discontinue radiotherapy prematurely (treatment policy estimand). The number of missing data will be reported. The point estimate of the rate of decrease and the associated 95% confidence interval will be presented. To test whether the rate of decrease is significantly > 10%, the one-sided binomial test at a one-sided 2.5% significance level will be applied.

To further assess the impact of other factors on the primary endpoint, stratified analyses will be conducted. Factors of particular interest include sleep disorders at baseline and use of smartphones or tablets at bedtime. Furthermore, a logistic regression model including the sleep disorder rating scale at baseline, use of smartphones or tablets at bedtime and other factors such as age, type of breast surgery, systemic anticancer treatment, body mass index and co-morbidity will be fitted to identify significant predictive factors for decrease of sleep disorders. Adjusted odds ratios and 95% confidence interval (Wald χ2) will be derived.

In addition, each component of the primary endpoint will be subjected to statistical analyses to evaluate sleep disorders during the study using descriptive statistical methods. These analyses allow detailed assessments of the scales over time considering potential decrease and increase in sleep disorders. For graphical visualization, Spaghetti-plots and Box-Whisker diagrams will be provided. Changes from baseline will be considered and subjected to descriptive analyses. Friedman and Wilcoxon-signed rank tests may be applied to compare study visits. Cumulative distribution plots of changes from baseline at each visit will be presented; they display a continuous change from baseline on x-axis and the cumulative percentage of patients experiencing that change on y-axis. Analyses will be further stratified by sleeping disorders at baseline and use of smartphones at bedtime. For further exploratory analysis, rates of patients experiencing sleep disorders at each time will be estimated together with associated confidence intervals. These analyses will also be stratified by sleeping disorders at baseline and the use of smartphones at bedtime.

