### Sample size calculations

The main goal of the study is to evaluate sleep disorders in breast cancer patients prior to and during a course of radiotherapy in terms of severity of sleep disorders, distress caused by sleep disorders and use of sleeping drugs. This will allow to evaluate the potential effect of habituation to radiotherapy during the course of treatment and generate hypotheses. Forty-eight patients with documented start of radiotherapy, a documented completed questionnaire at baseline, and at least one completed questionnaire during radiotherapy are subjected to statistical analysis. Assuming that 5% of patients do not fulfil the requirements, 51 patients should be enrolled. This sample size is set at the maximum that is deemed achievable in this study within the timeframe given the size of the target population.

With this sample size, a one-sided exact test for one binomial population with a significance level of 2.5% has a power of 80% to yield statistical significance if the rate of patients with improvement (decrease) of sleep disorders during the radiotherapy compared to baseline is 25% (rate under the alternative hypothesis) and specifying a decrease of 10% as non-causal change in this uncontrolled study setting (null hypothesis). With an improvement rate of at least 28% under the alternative hypothesis, the statistical test with this sample size achieves a power of at least 90% (calculated with StatXact, Version 11, Statistical software for exact nonparametric inference, Cytel Software, Cambridge, MA, USA).

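### The only stated risk-factor model is a seven-predictor logistic regression with about 12 expected responders; adding a baseline-adjusted model of the 0–10 scores would use the same data better

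*Protocol article*

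**What the plan says.** The primary analysis (Protocol article, Statistical methods for investigated endpoints) tests "the dichotomized composite endpoint" after 15 fractions against a 10% rate. The same section then turns to factors that may influence this endpoint. It plans stratified analyses and "a logistic regression model including the sleep disorder rating scale at baseline, use of smartphones or tablets at bedtime and other factors": age, type of breast surgery, systemic treatment, body mass index and co-morbidity. The model's purpose is to find significant predictors of improvement, reported as adjusted odds ratios with Wald 95% intervals.

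The individual components are handled differently: "Changes from baseline will be considered and subjected to descriptive analyses". Plots and summaries are split by baseline sleep disorders and smartphone use at bedtime, and rates of sleep disorders with confidence intervals are split the same way. The optional Friedman and Wilcoxon signed-rank tests compare visits, not device groups. Under Assessments, the article says that the factors will be correlated with sleep disorders but names no method.

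The analysed sample is "Forty-eight patients with documented start of radiotherapy, a documented completed questionnaire at baseline, and at least one completed questionnaire during radiotherapy". Under Questionnaires, both 0–10 scales are completed at each time point by patients who have sleep disorders. The Discussion singles out electronic media as a special focus. It and the abstract say that patients should be advised to change bedtime device use if it proves to be a risk factor.

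**The concern.** The article commits the device question to a yes/no outcome with few events and many predictors, although two graded scores are collected at baseline and at 15 fractions. Cutting a score at a threshold loses information, and seven or more coefficients on about 12 responders makes Wald inference fragile. A real device effect could be missed, or the fit could fail, when the same questionnaires support a more sensitive analysis. Sample size cannot compensate, because the article says that the number is the most that can be recruited. Since advice to patients is tied to whether device use emerges as a significant factor, the analysis behind that statement should be the most informative one available.

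**Working it through.** **1. The plan's own figures.** Inputs from Sample size calculations: 48 analysed patients, null rate 10%, alternative 25% (or 28%), one-sided 2.5%, 5% not evaluable.
- The exact test rejects at 10 or more responders of 48: P(X ≥ 10 | 10%) = 0.0187.
- Power is 79.5% at 25% and 90.1% at 28%.
- Enrolment: 48 / 0.95 = 50.5, so 51.

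All agree with the article. The primary test is not in question.

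**2. Events available to the logistic model.** 48 × 0.25 = 12 responders. The named predictors are baseline rating, device use, age, surgery, systemic treatment, body mass index and co-morbidity: seven, if each takes one coefficient. 12 / 7 = 1.7 responders per predictor.

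**3. Information kept by a cut.** For a normal score cut at its 25% point, relative efficiency is φ(z)² / [p(1 − p)]. With p = 0.25, z = −0.674 and φ(z) = 0.318, this is 0.101 / 0.1875 = 0.54. About 46% is lost, before crediting the composite with what distress and drug dose add.

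**4. Closed-form check.** Two groups of 24, device effect 0.8 SD, two-sided 5%, overall response 25%. Responder rates are then 12.9% in users and 37.1% in non-users.
- Means: Φ(0.8 × √(24/2) − 1.96) = Φ(0.81) = 79%.
- Proportions: null SE √(0.25 × 0.75 × 2/24) = 0.125; alternative SE √[(0.129 × 0.871 + 0.371 × 0.629)/24] = 0.120; Φ[(0.242 − 1.96 × 0.125)/0.120] = 49%.
- Ratio 0.62. With 30% device use the same formulas give 72% and 32%, ratio 0.45.

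**5. Simulation of the stated model.** A seven-predictor Wald logistic model on the composite was compared with a linear model of the 15-fraction severity score on the same seven predictors (n = 48, two-sided 5%, 1,000 to 1,500 runs per setting). Monte Carlo SE is at most √(0.25/1,000) = 1.6 percentage points. Separated or failed logistic fits counted as not significant.

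Assumptions, none from the document: baseline mean 5 and SD 2, residual SD 1.5–2.0, baseline slope 0.5–0.8, severity–distress residual correlation 0.3–0.9, device use 30–70%, effect 0.5–1.0 SD. No rate of sleeping-drug reduction was among them, so that component's contribution is not quantified.

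Results at 0.8 SD:

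| Device use | Response | Users improve | Logistic | Score model | Ratio |
|---|---|---|---|---|---|
| 50% | 25% | less | 38–42% | 67–71% | 0.56–0.59 |
| 30% | 25% | less | 12–13% | about 61% | about 0.2 |
| 70% | 25% | less | 43.3% | 62.7% | 0.69 |
| 30% | 25% | more | 41.2% | 63.0% | 0.65 |
| 50% | 35% | less | 52.2% | 68.5% | 0.76 |
| 30% | 50% | less | 45.5% | 61.4% | 0.74 |

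At 50% use and 25% response, a baseline slope of 0.5 gives 30.5% against 66.9% (ratio 0.46). A severity–distress correlation of 0.9 gives 34.6% against 69.0% (ratio 0.50). Over effects of 0.5 to 1.0 SD, the ratio goes as low as about 0.15 (30% use, 25% response, users improving less) and as high as 0.92 (30% use, 50% response, 0.5 SD). With a device effect present, the logistic fit failed or separated in about 5–12% of runs at 50% use and 16–35% at 30% use. The score model had more power in every setting with an effect.

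**The case against.** The article calls its analyses largely descriptive and exploratory, aims to generate hypotheses, sets its sample size by feasibility and claims no power for any risk factor. A logistic model of the study's own primary endpoint contradicts nothing, and further models may stand in an analysis plan that is not shown. That rightly limits the weight of the point. It does not remove it, because the article itself fixes the outcome, the covariates and the Wald inference for a declared focus.

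Several stronger readings are tempting and are not supported:
- *That this is the only inferential look at risk factors.* Stratified analyses of the primary endpoint and stratified rates with confidence intervals are also planned, and the scores will be displayed by device group. What is absent is a stated between-group model of the scores.
- *That dichotomising discards most of the information.* The loss is about 46% under normality, and the composite recovers some of it. With distress included, under a different set of assumed values, two-predictor logistic power was 24% against 44% for the score model at 1 point, and 40% against 78% at 1.5 points.
- *That power is simply halved.* That is near the middle for 25% response and 50% device use, but it is not a fixed result.
- *That moderate effects would be found with a score model.* If SD is 2.5 and test–retest correlation 0.7, residual SD is 2.5 × √(1 − 0.7²) = 1.79. A 1.5-point difference is then 0.84 SD, which is large. At 0.5 SD the closed-form two-group powers are 23% and 41%, so both approaches are more likely to miss such an effect.

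A practical objection also stands. The scales are completed only in case of sleep disorders, so patients whose problem resolves may have no follow-up score. In one run, dropping zero scores cut the score model's power from 77% to 63% for a device effect of −1.5 points. A score model therefore needs a rule for these patients.

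**Conclusion.** The point holds as a worthwhile, inexpensive improvement to a secondary exploratory analysis. The facts in the document are firm: one stated regression, at least seven predictors, a dichotomised outcome, 12 responders expected at the planning rate, and scores compared by device group only descriptively. The size of the gain is conditional. It is about 40% against 70% power at 50% device use, 25% response and 0.8 SD, with a ratio of about 0.15 to 0.9 across the assumed settings. The direction is consistent throughout. Nothing here touches the primary endpoint or its binomial test, and a score model does not make 48 patients sufficient for small device effects.

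**What to change.** Leave the primary endpoint and the binomial test unchanged. In Statistical methods for investigated endpoints:
- Add a prespecified linear model (ANCOVA) of the 15-fraction severity score on baseline severity and bedtime smartphone or tablet use, with at most one or two further named factors.
- Repeat it for the distress score as supportive.
- Report mean differences with 95% confidence intervals, using robust or bootstrap standard errors because the scale is bounded.
- State that patients who report no sleep disorders at follow-up are scored 0 on both scales.
- Keep the logistic model alongside, report the sleeping-drug component separately, and label all of these analyses exploratory.

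The cost is wording only; no new data or patients are needed. The downsides are that results are in scale points rather than odds ratios, the score model does not cover drug dose, and a second outcome model adds another exploratory comparison.

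### The exploratory seven-predictor logistic model has about 12 expected improvers; ordinary fitting with Wald intervals inflates its odds ratios and sometimes gives none, and Firth penalisation would largely repair this

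*Protocol article*

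**What the plan says.** Under *Statistical methods for investigated endpoints*, the Protocol article plans a logistic regression of the dichotomised composite. The predictors are the baseline sleep rating, bedtime smartphone or tablet use, and further factors of which five are given as examples: age, kind of surgery, systemic therapy, BMI and co-morbidity. The model "will be fitted to identify significant predictive factors for decrease of sleep disorders". Adjusted odds ratios are to carry 95% intervals of Wald type. No penalised, exact or profile-likelihood method is mentioned, so ordinary maximum likelihood is the natural reading. The same section calls the analyses mainly descriptive and exploratory, and plans stratified analyses by baseline sleep disorder and device use.

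Under *Sample size calculations*, the analysis rests on "Forty-eight patients with documented start of radiotherapy, a documented completed questionnaire at baseline, and at least one completed questionnaire during radiotherapy". The power statement applies "if the rate of patients with improvement (decrease) of sleep disorders during the radiotherapy compared to baseline is 25" per cent. The sample is described there as the largest that can be achieved.

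The Abstract and the Discussion both say that patients should be advised to change their bedtime device use if it proves to be a risk factor. The Discussion adds the word significant.

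**The concern.** In logistic regression the information lies in the smaller outcome group, here the improvers. With so few of them and at least seven coefficients, two things go wrong with ordinary maximum likelihood. Estimates of real effects are pushed away from an odds ratio of 1. In some data sets a combination of predictors splits improvers from non-improvers completely or almost so (separation), and then no finite estimate or Wald interval exists for the coefficients involved.

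This is the only adjusted analysis described for the risk-factor question, which includes the smartphone question in the study's title. An exaggerated odds ratio from it could be carried into what patients are told.

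**Working it through.** **1. The design figures reproduce.** Inputs from *Sample size calculations*: n = 48, null rate 10%, alternative 25% (second scenario 28%), one-sided 2.5%, 5% not evaluable.

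- The smallest r with P(X ≥ r | 48, 0.10) ≤ 0.025 is r = 10, with exact level 0.0187.
- Power at 25%: P(X ≥ 10 | 48, 0.25) = 0.795 (stated 80%). At 28%: 0.9005 (stated at least 90%).
- Enrolment: 48 / 0.95 = 50.5, so 51 (stated 51).

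**2. Improvers per predictor.** With seven predictors:

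- At 25%: 48 × 0.25 = 12; 12 / 7 = 1.7.
- At 28%: 48 × 0.28 = 13.4; 13.4 / 7 = 1.9.
- Ceiling, when half improve: 24 / 7 = 3.4. Beyond 50% the non-improvers become the smaller group, so no rate does better.

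**3. Simulation.** The article gives no covariate distributions or effect sizes, so these are assumptions. Setting: n = 48, 25% improved, three continuous and four binary independent predictors, true log odds ratio 0.5 per SD of baseline rating and −0.7 for device use, other effects zero, 1,500 runs per row. Prevalences are listed in the order device use, surgery type, systemic therapy, co-morbidity. Maximum-likelihood (ML) means are over non-separated runs. All other columns concern device use, apart from separation.

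| Prevalences | Separated, 7 predictors | Mean log OR, ML | Mean log OR, Firth | Upper/lower CI ratio, ML | CI ratio, Firth |
|---|---|---|---|---|---|
| 0.5, 0.2, 0.4, 0.5 | 9% | −0.90 | −0.69 | 29.5 | 22.0 |
| 0.5, 0.1, 0.3, 0.2 | 38% | −0.90 | −0.69 | 28.0 | 21.6 |
| 0.7, 0.1, 0.85, 0.3 | 42% | −0.88 | −0.69 | 31.4 | 25.1 |

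The CI ratios are exp(3.92 × median standard error). The Firth ratios therefore use Wald-type standard errors and only approximate profile intervals.

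- *Inflation, device use:* 0.90 / 0.70 = 1.29 and 0.88 / 0.70 = 1.26. With a true odds ratio of 2 (log 0.69), ML means were 0.91 to 0.94, that is 0.91 / 0.69 = 1.32 to 0.94 / 0.69 = 1.36. A mean log value of 0.91 corresponds to an odds ratio of 2.5 where the truth is 2.
- *Inflation, baseline rating:* ML means 0.66 to 0.70 against 0.5, so 32 to 40%.
- *Spread:* SD of the device-use log odds ratio about 1.0 with ML and about 0.8 with Firth.
- *Separation:* about 3% when all binary factors are common, 7 to 11% when the rarest level is 20%, and 30 to 46% when it is about 10%. Three further binary predictors raise it from about 10% to 30% in the balanced setting. At a 40% improvement rate it is 1 to 3% (balanced) and 17 to 25% (a rare level).
- *Two predictors only (ML):* separation 0.3 to 0.7%, mean device-use log odds ratio −0.71 to −0.76, CI ratio 18 to 20.

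**4. What a significant result would need.** With the median ML standard error of 0.86, significance requires |log OR| > 1.96 × 0.86 = 1.69, an odds ratio above 5.4 or below 0.19. A real odds ratio of 2 or 0.5 that reached significance would therefore be reported as far too large an effect.

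**The case against.** Several stronger readings are tempting, and the material does not support them.

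- **Separation would be frequent.** That depends on prevalences the article does not give. With common factor levels it is a few per cent; only a rare level or a longer predictor list makes it frequent.
- **The Wald intervals mislead, or produce too many false positives.** In fits that converge, coverage was about 93 to 98%, and per-factor false positives were 4 to 6%. At least one of seven null factors was significant in 25 to 28% of fits, but that is ordinary multiplicity: seven independent 5% tests give 1 − 0.95^7 = 30%. The intervals are very wide or absent, not too narrow.
- **Overloading causes the low power.** For odds ratios of 2 and 3, seven predictors gave 15% and 30% power, and two predictors gave 14% and 29%. The limit is the sample size, which the article openly calls the maximum achievable.
- **The smartphone question rests on this model alone.** Stratified analyses of the primary endpoint, and of the full scales, by device use are also planned.
- **The model must be cut to two factors.** This is a trade-off. It would drop age, which the Discussion links to insomnia.

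It can also be said that the predictor list is illustrative and that a SAP may settle coding and non-convergence. This stands for those details. It does not remove the point, because the article itself states the model, its purpose and the Wald method. The exploratory label lowers the stakes, but sits uneasily with a search for significant factors and with the advice to patients.

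**Conclusion.** The point holds as a fault in a stated secondary, exploratory analysis. With about 12 improvers for at least seven predictors, and no improvement rate that lifts the ratio above 3.4, ordinary maximum likelihood gives device-use effects inflated by about 25 to 35% on the mean log scale and, in some data sets, no estimate at all. The improver count follows from the article's own figures, provided all 48 patients have the 15-fraction outcome. The size of the inflation and above all the separation rate (about 3% to over 30%) rest on assumed covariate distributions and effects. The inflation concerns real effects only; where a factor has no effect there is no systematic bias. The primary binomial test and its sample size stand. The method should be changed before analysis, but the study's main conclusion does not depend on it.

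**What to change.** 1. Keep the stated model, but fit it by Firth-penalised logistic regression with profile-penalised-likelihood 95% intervals in place of maximum likelihood with Wald intervals. In the simulations this gave finite estimates in every run and almost removed the bias (mean −0.69 against −0.70 for device use).
2. Close the predictor list before analysis, since each added factor makes the problem worse.
3. Add, as a sensitivity analysis, a model with only baseline rating and bedtime device use, the two factors the article singles out. This gives 12 / 2 = 6 improvers per predictor.
4. Report all factors as exploratory estimates with intervals. Drop the aim of identifying significant predictive factors, and do not present this model as support for advice to patients; align the Abstract and Discussion wording accordingly.

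The cost is a change of analysis wording, standard software, a little extra analysis work and slight shrinkage of the estimates. It does not buy precision: the limits for device use would still differ about 18- to 25-fold, and power stays low.

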### Data management and monitoring

Similar to a previous study, patients can be identified only by an individual number and their month/year of birth [10]. Data will be handled in accordance with the General Data Protection Regulation and German regulations for radio-protection. Study results will be published in a peer-reviewed journal involving a professional statistician and using the acronym RADIO-SLEEP.

## Discussion

Adjuvant radiotherapy is mandatory after breast-conserving surgery for primary breast cancer and is indicated also after mastectomy if the patients have risk factors for a local or loco-regional recurrence [2]. The situation that a patient has to undergo radiation treatment can cause psychological distress, which is often associated with sleep problems. Occurrence of sleep disorders varies between different types of cancer. In a previous study, patients with breast cancer reported significantly higher rates of sleep disorders, sleep disturbance and fatigue than patients with prostate cancer [11]. Moreover, in a post-hoc analysis of a randomized trial including 823 patients with different types of cancer (49% breast cancer patients) receiving chemotherapy, the proportion of patients with symptoms of insomnia and patients who met the criteria of insomnia syndrome were about three times higher than in the general population [12]. In this study, breast cancer patients reported higher number of sleep disorders than patients with other types of cancer.

Uncertainty exists whether sleep disorders decrease during a course of anticancer treatment due to an effect of habituation to the treatment procedures, or whether disorders increase due to treatment-related side effects and associated clinical symptoms. In a study of breast cancer patients, insomnia was significantly mediated by acute toxicities of chemotherapy or radiotherapy [6]. Since the risk of radiation-related side effects likely decreases with the use of modern high-precision radiotherapy techniques, the effect of habituation to the procedures of radiotherapy during a course of treatment may become stronger resulting in a decrease of sleep problems. This hypothesis is supported by the study of Thomas et al. that investigated changes in sleep during a course of radiotherapy and up to 6 months thereafter in patients with breast cancer or prostate cancer [5]. Both patient groups reported most sleep disorders before and during the first part of their radiation treatment. Additional studies are required to properly answer the question whether sleep problems increase or decrease during a course of radiotherapy. The RADIO-SLEEP study evaluates a potential decrease of sleep disorders due to habituation to radiotherapy in patients irradiated for primary breast cancer. Decrease of sleep disorders will be measured using a composite endpoint considering severity of sleep disorders, distress caused by sleep disorders and the use of sleeping drugs. Data after 15 fractions/3 weeks of radiotherapy will be compared to the data at baseline before radiotherapy (primary endpoint). The data are obtained from questionnaires completed by the patients, which included two self-rating scales and information about intake of sleeping drugs.

Moreover, the RADIO-SLEEP study investigates potential risk factors for sleep disorders. In a retrospective study of 175 breast cancer patients receiving adjuvant radiotherapy, occurrence of sleep disorders was significantly associated with higher distress scores, need for psychological support, and greater numbers of emotional, physical or practical problems [4]. Younger age was previously reported to be significantly associated with insomnia in the above-mentioned post-hoc analysis of patients receiving chemotherapy for different cancer types [11]. In a study of breast cancer patients treated with aromatase inhibitors, younger age showed a trend toward increased insomnia [13]. In another study of breast cancer patients, a high insomnia severity index was more common in patients receiving adjuvant chemotherapy than in those receiving adjuvant radiotherapy [14].

A particular focus of the RADIO-SLEEP study is on the impact of electronic media on sleep disorders. The patients complete a questionnaire regarding the use of such devices in general and specifically at bedtime. Negative associations of the use of electronic media at bedtime on sleep quality have been reported for adolescents and adults in general but not particularly for cancer patients [15–19]. Therefore, the RADIO-SLEEP study includes the use of smartphones or tablets at bedtime as a potential risk factor for sleep disorders in the investigated cohort of breast cancer patients.

If the RADIO-SLEEP study demonstrates a decrease of sleep disorders during the course of adjuvant radiotherapy for primary breast cancer, this aspect should be included in the pre-radiotherapy consent discussion with the corresponding patients. Moreover, if additional risk factors for sleep disorders are identified, this will likely lead to earlier psychological support for the patients. If the use of smartphones or tablets at bedtime is identified as a significant risk factor, patients should be advised to change this behavior.

